| Efficacy evaluation | # A self-reported hot flush diary completed daily  - The daily occurrence of hot flashes and their severity, rated on a scale from 1 (mild) to 4 (very severe), are recorded together.  - The daily hot flush score is derived by multiplying the frequency of symptoms by their severity. The average score over a week is then computed, and after 4 weeks of treatment, the efficacy of desvenlafaxine in reducing hot flash symptoms is evaluated in terms of both presence and degree of reduction. |
| Safety evaluation | Adverse events, lipid tests, and urine tests |
| Expected impacts and anticipated results | While hot flashes in the general population can often be treated with hormonal therapy, this approach is not viable for breast cancer patients specifically, as the use of hormonal therapy can increase the risk of further cancer progression.  Desvenlafaxine does not affect cancer progression and shows no drug interactions with Tamoxifen, making it safe for use. Consequently, it holds promise as an effective treatment for hot flashes in breast cancer patients on Tamoxifen.  This study is a randomized, double-blind, placebo-controlled trial designed to evaluate the efficacy of Desvenlafaxine as an alternative to hormonal therapy in these patients.  Additionally, through blood tests for estradiol, FSH, and AMH, as well as association analyses with the estrogen receptor gene and serotonin transporter gene, we aim to establish a biological foundation for predicting risk factors and treatment responses to hot flashes in breast cancer patients on Tamoxifen. |

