**2) Placebo**

- Starchy tablet, identical in appearance to *Pristiq*

1. **Inclusion criteria, exclusion criteria, number of study participants targeted and rationale for calculation**
2. **Inclusion criteria**

- Women, age 19 years or older
- Diagnosed with atypical ductal hyperplasia, ductal carcinoma in situ, lobular carcinoma in situ, or invasive breast adenocarcinoma stages I through IV.
- Taking tamoxifen regularly (6+ times/week) following the termination of surgery, chemotherapy, and/or radiation therapy due to breast cancer
- Moderate to severe hot flashes occurring 14+ times/week (on average, 2+ times/day) lasting for more than a month.

1. **Exclusion Criteria**

- Pregnant or breastfeeding
- History of seizure or hepatic/renal dysfunction
- Receiving any hormone therapy (including estrogen-/progesterone-/androgens-containing agents) or taking corticosteroids
- Use of antidepressants such as gabapentin, pregabalin, or clonidine to address depression and/or hot flash symptoms.
- Currently suffering from or having a history of severe psychiatric symptoms, such as hallucinations and delusions, mania, and high suicide risk

1. **Number of participants targeted and rationale for calculation**

This study aimed to determine whether the use of desvenlafaxine in patients suffering from hot flashes reduces its symptoms.

The primary endpoint was defined as the percentage reduction in hot flush symptoms = (symptom score at week 4–symptom score at a week before treatment) / symptom score at a week before treatment), and the following assumptions were made to calculate the number of participants to fulfil the primary outcome of the study.

① Level of significance, α = 0.025

The study was divided into three groups (50 mg, 100 mg, placebo), and a type 1 error was defined as 0.025 to determine whether there was a significant difference between the Desvena 50 mg treatment group vs. the placebo group and the 100 mg treatment group vs. placebo group.

② Type II error (β) is set to 0.20, and the power of the test is maintained at 80%.

③ The hypotheses in this study are as follows (two-tailed test):

- Null hypothesis: There is no difference in the rate of reduction of hot flashes between the 50 mg vs. placebo groups or between the 100 mg vs. placebo groups.
- Alternative hypothesis: There is a difference in the rate of reduction of hot flashes between the 50 mg versus placebo or 100 mg versus placebo groups.

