The number of participants was calculated based on a comparison of the desvenlafaxine 100 mg group with the placebo group. In a similar study conducted previously on menopausal women complaining of hot flashes, the mean reduction rate was 0.8 and standard deviation (SD) 0.72 when desvenlafaxine 100 mg was administered, and in the case of the placebo group, the average reduction rate was 0.47 and standard deviation 0.79 [5]. The number of participants in the study that achieved 80% power at a 2.5% significance level was 101 in each arm, for a total of 303. The number of participants was planned to be 339 to account for a dropout rate of 10 %.

1. **Study participant recruitment plan**

Participants will be recruited by posting the [Notice of Recruitment of Research Subjects] in the outpatient departments of the haematology oncology and integrated care center, surgery, obstetrics/gynecology, and mental health clinic. In addition, participants will be recruited by posting a recruitment announcement on “https://cafe.naver.com/uvacenter/158559", the representative internet community of the Breast Cancer Patients' Association.

The principal investigator and funding agency will not exclude patients from participation in this study based on race or socioeconomic status. If the selection criteria for this study were met, every effort will be made to allow as many patients as possible to participate in this study.

1. **Study methods**
2. **Specific research methods**

|  | Baseline | Medication Period | | End of Medication | Tapering period |
| --- | --- | --- | --- | --- | --- |
| Period | T0 | T1 | T2 | T3 | 3days |
| Week | -1w | 0w | 1w | 4w | 4w + 3days |
| Day |  | 1 | 8 | 29 | 29–31 |
| Permissible range of visits |  | ±3 days | ±3 days | ±3 days |  |
| Informed consent | O |  |  |  |  |
| Randomization |  | O |  |  |  |
| Study Drug Administration |  | O | O |  |  |
| Medical record check | O |  |  |  |  |
| Physical Examination |  | O | O | O |  |
| Hot flashes diary | O | O | O | X |  |
| Self-reported questionnaires | O | O | O | O |  |
| Blood/urine tests |  | O |  | O |  |
| Assessment of adverse events |  | O | O | O |  |
| Medication adherence evaluation |  |  | O | O |  |
| Concomitant medication check | O | O | O | O |  |

This was a 4-week dosing, multicenter, randomized, double-blind, placebo-controlled trial.

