Participants will be randomized to receive desvenlafaxine or placebo for a total of 4 weeks + 3 days, maintain a daily hot flashes diary, and have a total of 4 clinic visits for four questionnaire assessments and two blood and urine tests. Height, weight, BMI, and blood and urine tests will be performed at T1 and T3.

The participants will complete an informed consent form at the initial visit, and an initial questionnaire assessment will be administered. If participants did not know the exact date of menstruation in the menstrual history assessment section and the date of breast cancer diagnosis in the cancer-related information section, the following are written: if participants remember only the month, write 15 days (e.g., October ?day 2017 -> October 15, 2017), and if participants remember the beginning, middle, and end of the month instead of the exact date, write 5, 15, and 25 days, respectively (e.g., early October 2017 -> October 05, 2017).

Afterwards, the participants are advised to maintain a hot flashes diary without medication for one week to assess the baseline status before medication. During the same period, patients will be randomized into the desvenlafaxine 100 mg, 50 mg, or placebo group by a third-party institution unrelated to the study (Medical Research Collaborating Center).

From one week after study registration, each of the three groups will be administered a dose of desvenlafaxine or placebo for four weeks. To reduce the adverse effects of abrupt discontinuation in the desvenlafaxine 100 mg group, there will be a 3-day tapering period with one tablet of desvenlafaxine 50 mg or one tablet of placebo.

During the administration period, the patients will complete a hot flashes diary and medication compliance assessments. After participating in the study, patients will receive a hot flashes diary form to record for 1 week, 1 week, and 3 weeks, at visits of -1, 0, and 1 week, and the data written by the patient during that period will be included in the case report form of the previous periods. During the above visits, a physical examination and assessment for adverse events and medication adherence will be performed.

Self-reported questionnaire assessments will be administered at visits 1 week prior to study enrollment and 0, 1, and 4 weeks after study enrolment. Moreover, blood and urine tests will be performed at 0 and 4 weeks after study enrollment.

1. **Control group setting and randomization method**

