Participants who provided written informed consent and fulfilled all inclusion and exclusion criteria for enrollment will be randomized in a 1:1:1 ratio to the desvenlafaxine 100 mg arm, desvenlafaxine 50 mg arm, and placebo arm.

A randomization table will be created to assign the participants to one of the three arms using a stratified block randomization method, and web-based allocation will be made according to the randomization table. The stratification factors are age (< 50 and >50 years), presence of depression (defined as a PHQ-9 score of 9 or more), and institution (Seoul National University, Seoul National University Bundang Hospital, National Cancer Center). The randomization table and web-based randomization will be managed and operated by the Medical Research Collaborating Center (MRCC) of Seoul National University/Seoul National University Hospital, which is independent of the study.

If a serious adverse reaction occurs in a participant after participating in the study, they will be withdrawn from the study and unblinded; in this case, the investigator will unblind the participant through a third-party institution (Medical Research Collaborating Center) that manages and operates the randomization.

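### A serious adverse reaction removes the woman from the study, not only from study drug, so one before week 4 costs her week-4 diary score and only post-baseline lipid and urine tests

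*Protocol*

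**What the plan says.** The last paragraph of the protocol section on control group setting and randomization method states: "If a serious adverse reaction occurs in a participant after participating in the study, they will be withdrawn from the study and unblinded". The code is broken through the independent centre (MRCC) that runs the randomization. The sentence is mandatory, it names the study rather than the study drug, and it has no exception.

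Three other parts of the protocol determine what such a woman loses:

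- **Primary endpoint** (sample size rationale): the percentage reduction needs the "symptom score at week 4" as well as the baseline score.
- **Diary** (Specific research methods): women receive a "diary form to record for 1 week, 1 week, and 3 weeks, at visits of -1, 0, and 1 week". Week 4 is the last week of the third form.
- **Laboratory tests**: "blood and urine tests will be performed at T1 and T3", repeated as "blood and urine tests will be performed at 0 and 4 weeks after study enrollment". The overview lists the lipid profile and urinalysis among these tests, and its safety evaluation row reads "Adverse events, lipid tests, and urine tests".

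The document shown has no early-termination visit, no test at withdrawal, and no diary or follow-up after withdrawal.

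**The concern.** Stopping a drug and leaving a trial are different events. A serious reaction is often a good reason for the first, but it is not in itself a reason for the second. This rule joins them. The women concerned had the most serious reactions, in a trial that asks about safety as well as efficacy. An analysis plan can say how missing values are handled, but it cannot restore diary days never filled in or samples never taken. The rule on who is followed is set in the protocol, so this is not a matter to leave to the analysis plan.

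The same sentence also breaks the code in every such case, whether or not anyone needs to know the treatment to care for the woman.

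**Working it through.** **1. The plan's own sample size.** Inputs from the sample size rationale: means 0.80 and 0.47 (difference 0.33), SDs 0.72 and 0.79, two-sided α = 0.025, power 80%.

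- Normal approximation: n = (2.241 + 0.842)² × (0.72² + 0.79²) / 0.33² = 9.505 × 1.1425 / 0.1089 = 99.7, so 100 per arm.
- With the t distribution, 101 per arm gives 80.0% power. This is the plan's figure.
- Dropout: 101 / 0.90 = 112.2, so 113 per arm and 339 in total, as stated.
- Allowance for dropout: (339 − 303) / 3 = 12 women per arm.

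The sample size reproduces, and the point does not depend on any error in it.

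**2. What is lost, by time of reaction.** Dosing covers days 1 to 28 and the taper covers days 29 to 31, which makes 31 drug days. T1 is day 1 and T3 is nominally day 29.

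| Reaction on | Week-4 score | T3 lipid and urine tests |
|---|---|---|
| Days 1–21 (21 of 31, 68%) | none | none |
| Days 22–28 (7 of 31) | part of the week at most | none |
| Days 29–31 (3 of 31) | complete | already taken |

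T1 is the visit at which dosing starts, so T3 is the only post-baseline sample. A woman withdrawn before T3 has no post-baseline lipid or urine result.

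**3. How many women.** The document gives no rate of serious adverse reactions. Assume 1% to 3% per arm, spread evenly over the 31 drug days, with 113 women per arm.

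- Whole week-4 score lost: 113 × 0.01 × 21/31 = 0.77; 113 × 0.03 × 21/31 = 2.30.
- T3 tests lost (and all or part of the week-4 score): 113 × 0.01 × 28/31 = 1.02; 113 × 0.03 × 28/31 = 3.06.

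At an assumed 0.1% to 0.5%, the whole-score losses are 113 × 0.001 × 21/31 = 0.08 to 113 × 0.005 × 21/31 = 0.38 women per arm. The T3 losses are 113 × 0.001 × 28/31 = 0.10 to 113 × 0.005 × 28/31 = 0.51.

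**4. Against the allowance.** The largest of these figures, 3.06 per arm, is well under the 12 per arm planned for dropout.

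**The case against.** The strongest reply is that the harm is inferred. The sentence closes the randomization section and mainly explains how the code is broken. It does not say that data collection stops, and silence elsewhere is weak evidence of what the sponsor intends. That is fair. A reader might infer that the protocol forbids further follow-up, and the text does not go that far. But withdrawal from the study normally means the end of study assessments, and nothing shown gives it another meaning. If only drug withdrawal was meant, the same edit makes that clear.

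Second, the numbers are tiny and rest on an assumed rate. A serious adverse *reaction* is narrower than a serious adverse event, and the objectives section describes the drug as safe in earlier trials. This stands, and it is why lower rates are shown above.

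Third, a reader might infer a loss of power. If 1% to 3% were lost on top of a full 10% dropout in both compared arms, power would fall from 80.3% to between 79.9% and 79.0%. That requires the allowance to be used up by other losses, counts part-week scores as wholly lost, and applies the same rate to placebo. The documents support none of this. Women withdrawn under the rule are dropouts, and dropouts are already allowed for.

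Fourth, follow-up after drug stop might seem essential because the protocol adds a taper "To reduce the adverse effects of abrupt discontinuation in the desvenlafaxine 100 mg group". This argument has limited reach. All active-arm women take 50 mg in week 1, the 50 mg arm goes straight to placebo in the taper, and the schedule has no assessment in the taper column for anyone. It applies mainly to 100 mg women after week 1.

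Finally, the reaction itself can still be recorded, and breaking the code after a serious reaction is a defensible safety choice. Both are true. What is questioned is doing it automatically, and it is not said to cause missing data.

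**Conclusion.** The point holds as an inexpensive improvement to a rule that the protocol states. Followed in its ordinary sense, the rule leaves a woman with a serious adverse reaction before week 4 without a week-4 diary score and without any post-baseline lipid or urine result. The number is probably very small: about 0.8 to 2.3 women per arm of 113 would lose the whole week-4 score if 1% to 3% react, evenly over the drug days, and fewer at lower rates. The reading of the word withdrawn is the main assumption, and the rate is the second.

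No loss of power is claimed. A reader might also infer that the efficacy comparison would be biased, because the losses may be related to treatment. That depends on analysis rules not shown here, so the document does not support it.

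**What to change.** Replace the sentence with:

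> After a serious adverse reaction, study drug is stopped as clinically indicated, with taper where appropriate. The code is broken through the MRCC only when knowing the treatment is needed for care. With her consent, the woman stays in the study, continues the diary to week 4, and attends T3 (including the planned blood and urine tests) and adverse-event follow-up; if she will not continue, the T3 tests are done at drug stop.

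Record the dates of drug stop and of any code break, so that scores and samples can be identified as on or off drug, and as blinded or not.

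The cost is a few sentences. The diary, the T3 visit and the code-break route already exist. A woman who reacts before the week-1 visit must still be given the 3-week diary form. The downside is that some women will decline, and some scores and samples will be off drug and possibly unblinded, so part of the information is recovered rather than all of it.
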